### e-couch platform usage data

Participants who complete baseline assessments and meet all eligibility criteria will be issued a unique login token, providing them with free access to the e-couch platform. These tokens will allow participants to create an account and engage with the e-couch intervention modules.

Cumulative usage data associated with each participant’s token will be collected throughout the study period. We will manually download these data from the e-couch administrative platform approximately once per week. Each download will include updated cumulative usage information for all participants.

Examples of the data to be extracted include general platform activity (such as number of logins, registration and last login dates, total time spent on the platform, and first and last access dates), as well as module-specific engagement metrics (such as progress status, time spent within each module, and number of accesses). These data are automatically logged by the platform and reflect participants’ lifetime engagement with the intervention. While additional variables are available through the platform, only a predefined subset relevant to the study will be extracted, and not all extracted variables will necessarily be used in the final analysis.

As the data are system-generated, no assessor training is required. The reliability and validity of the usage data are determined by the platform’s internal tracking mechanisms. A codebook detailing all available data fields is maintained by the platform provider and can be made available upon request.

### Processes to promote quality of data collection

To promote data quality, we will implement several procedures, including attention checks, identity verification, and study engagement checks. Participants will be excluded if they demonstrate inconsistencies in their self-report information during the identity check, show inattentive task performance, or lack engagement with the study (e.g., fail to provide timely replies to study emails). These procedures are described in detail below.

#### Attention checks

We will implement several attention checks within the self-report questionnaires and will employ the Matrix reasoning task as a way to measure random task behavior. We will have three attention-check questions in two self-report questionnaires (PHQ-9 and WHOQOL-BREF) at the beginning of the study. For example, we will ask “*How well are you able to touch the peak of Mount Everest with your hands right now?*”, where participants are expected to only answer “*Not at all*”. We will also use task behavior in the matrix reasoning task to assess whether participants are paying attention during the tasks. If participants answer fewer than three answers correctly in the matrix reasoning task (i.e., below chance level), or respond to more than six questions in 3 seconds (suggesting they are not thinking the problems through), they will be marked as failing the matrix reasoning task. If participants fail more than one of four (three attention check questions and matrix reasoning task) attention checks within the first five minutes of the study, they will be excluded from further participation in the study. Participants will be notified that if they believe they had been excluded by mistake or due to technical issues, they can contact us for an identity check and to explain the situation. We will invite them back to the study upon successful completion.

#### Identity check

Participants who successfully pass the attention checks may be invited to a brief zoom call with the experimenters to verify their identity. We will randomly invite approximately 20% of participants recruited through ResearchMatch (given that in our experience they are a reliable recruitment platform) and all participants recruited through other channels. Once invited, participants will have two weeks to book a time-slot for the 5-minute zoom meeting. During the zoom meeting, we will ask participants for basic information they had provided in the screener or demographics questionnaire and compare their verbal answers to the ones previously provided. We will also ask them to show a photo ID to the camera for verification of information such as location and age. We will exclude participants from the study if there are multiple mismatches between the information they provide and their screener responses, or if they fail to schedule a zoom meeting within the required timeframe. In these cases, we will also withhold payment for their time in the study so far, as we cannot verify their identity in order to determine whom we should compensate. Note: this procedure is updated from protocol version 1.0, which did not include identity checks (see **Supplement *Protocol changes***).

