### Exclusion after starting the study

Once participants have enrolled in the study, we will exclude those who fail the zoom identity check, demonstrate inattentive task performance, or show insufficient study engagement (see Section 25, *Data collection method: Processes to promote quality of data collection*, for details).

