**Figure 1 f1:**
[figure not shown]
Schematic diagram of study design and participant timeline.

At baseline, participants will complete QB1 (clinical symptom measures and a matrix reasoning task; approximately 35 minutes). They will then proceed to TB1 (four behavioral tasks; approximately 65 minutes) and after one day, to TB2 (two behavioral tasks; approximately 40 minutes). After completing TB2, participants will be randomly assigned to either the BA or CR group in a 1:1 ratio and can begin their five-week engagement with the e-couch program. Each module or submodule will require approximately up to 30–60 minutes per week, and participants will be encouraged to practice skills for a full week before progressing to the next module (see Section 15a, *Intervention and Comparator* for e-couch schedule).

While working through e-couch, participants will also complete additional assessments and behavioral tasks. Before starting e-couch week 2, they will complete QB2 (clinical symptom measures; approximately 7 minutes). Before e-couch week 4, they will complete TB3 (same questionnaires as in QB2 and four behavioral tasks; approximately 70 minutes). At the end of five weeks of e-couch, participants will complete QB3 (clinical symptom measures; approximately 30 minutes) to assess post-intervention symptoms.

Follow-up of symptoms will be assessed with questionnaires at 6, 18, and 42 weeks after study completion to assess immediate, mid-term, and long-term effects of the e-couch intervention. Each questionnaire will take approximately 7 minutes. For detailed description of the questionnaires and behavioral tasks, see **Figure 2** and Section 25, *Data collection method*.

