#### Implementation (23)

All major components of the study will be fully automated (see Section 26, *Data management*, for a detailed description of the automated state machine that will govern participants’ progression through the study). The following sequence describes the automated study procedures: Participants will first complete a screening questionnaire. Those who meet eligibility criteria will automatically receive an email invitation to the main study. After providing informed consent, they will receive access to the baseline assessments. Upon completion of all baseline measures (QB1, TB1, TB2; **Figure 1**), participants will be assigned to the CR or BA group using a random number generator on the central computer. This assignment will be recorded in the study database linked to the state machine that defines each participant’s path through the study, and in a separate backup document. Immediately after randomization, participants will receive automated instructions via email specifying which module of e-couch to complete for week 1. In each subsequent week, they will receive further automated emails with instructions on any assessments to complete and which module of e-couch to complete. After completing QB2, participants will be informed regarding which intervention group they are assigned to. All information stored in the database and on the study server will be backed up daily through automated IT processes. The backups will not be accessible by members of the research team. In addition, all email communication will be saved in a log file and backed up by IT processes on separate Princeton servers.

As such, no personnel will be involved in manually enrolling participants, assigning them to interventions, or delivering the interventions. The only aspects of the study that will be handled manually are identity verification of participants, payment processing (i.e., manually sending Amazon gift cards to participants based on calculations from our automated system), and responding to participant-initiated emails or phone calls (e.g., extension requests, troubleshooting, or clarification questions). Personnel cannot manually enroll participants or assign them to groups. If study team members were to make manual changes *post hoc*, these would lead to mismatches across our backed-up records.

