### Who will be included in the analyses (27b)

For all analyses, we will include only participants who (a) met the assessed inclusion and exclusion criteria specified in Section 14a, *Eligibility criteria*, and (b) passed identity and attention checks at the beginning of the study. For predictive modeling and causal inference, the analytic sample will include participants who were randomized and had a baseline PHQ-9 total score greater than 4. This constitutes our intention-to-treat (ITT) sample.

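### Randomisation does not wait for the identity check, so the plan as written allows identity-check exclusions after allocation from the sample it calls intention-to-treat

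*Protocol article*

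**What the plan says.** All references are to the protocol article.

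- **Randomisation trigger.** Sequence generation (21) assigns the arm when TB2 is completed. Implementation (23) says the same: "Upon completion of all baseline measures (QB1, TB1, TB2; Figure 1), participants will be assigned to the CR or BA group". E-couch instructions go out straight afterwards. Neither section mentions the identity check.
- **Pace of baseline.** Participant Timeline (18) has QB1, then TB1, "and after one day, to TB2 (two behavioral tasks; approximately 40 minutes". Each batch may take seven days, with an automatic further week.
- **Identity check (25).** "Participants who successfully pass the attention checks may be invited to a brief zoom call with the experimenters to verify their identity". For ResearchMatch, "We will randomly invite approximately 20% of participants recruited through ResearchMatch"; everyone from other channels is invited. "Once invited, participants will have two weeks to book a time-slot for the 5-minute zoom meeting". People are excluded for multiple mismatches, a number left undefined, "or if they fail to schedule a zoom meeting within the required timeframe".
- **Consequence.** Exclusion after starting the study: "Once participants have enrolled in the study, we will exclude those who fail the zoom identity check". Section 27b limits all analyses to people who, among other conditions, "passed identity and attention checks at the beginning of the study", and calls the resulting randomised sample with PHQ-9 above 4 intention-to-treat.
- **Disclosure.** Participants learn their arm after QB2, which precedes e-couch week 2 (sections 18 and 23).
- **Who runs the check.** Section 23 lists identity verification among the few manual steps. Data storage and security (26) keeps group assignment and identity-check assignments in one metadata database. Blinding (24) does not mention the staff who make the calls.

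**The concern.** An eligibility check that depends only on facts fixed before allocation can be applied late without biasing the comparison, provided that it is judged blind to arm. Not booking a call is different. It is something a participant does or fails to do, and if it happens after allocation it may reflect how the study is going for that person. Under 27b it nevertheless counts as failing an entry check, so the person leaves the analysis set altogether and is not counted as a randomised participant with a missing outcome.

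The protocol expects week-6 outcomes to be possibly missing not at random (27c) and promises sensitivity analyses for that (27d). Someone removed under the identity check need never appear in those analyses. The personalized advantage index comparison in 27a and the per-assignment analysis in 27d both rely on the randomised groups staying intact.

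**Working it through.** The protocol gives no figure for this point, so the check sets its own timings side by side.

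**Inputs.** Booking window of 14 days (Identity check, 25). TB2 one day after TB1; seven days per batch plus an automatic seven (section 18). Arm told after QB2, before e-couch week 2, taken as about 7 days after randomisation (sections 18 and 23).

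**Assumption.** The invitation comes on day 0, right after the attention checks in the first five minutes. The protocol does not fix this date; a later invitation moves the deadline later by the same number of days.

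**Formulas.** Booking deadline = 0 + 14 = day 14. At *d* days for each of the three baseline batches, randomisation is on day 3*d* and disclosure on about day 3*d* + 7. On the fastest path QB1 and TB1 are done on day 0 and TB2 on day 1, so randomisation is on day 1 and disclosure on day 1 + 7 = 8.

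| Pace | Randomised (day) | Arm told (day) | Deadline minus randomisation | Deadline minus disclosure |
|---|---|---|---|---|
| Fastest | 1 | 8 | 14 − 1 = 13 | 14 − 8 = 6 |
| 3 days per batch | 9 | 16 | 14 − 9 = 5 | 14 − 16 = −2 |
| 7 days per batch | 21 | 28 | 14 − 21 = −7 | 14 − 28 = −14 |
| 14 days per batch | 42 | 49 | 14 − 42 = −28 | 14 − 49 = −35 |

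The deadline falls after randomisation when 3*d* < 14, that is, below about 4.7 days per batch. It falls after disclosure when 3*d* + 7 < 14, that is, below about 2.3 days per batch. The deadline governs booking only, so the call itself can come later still.

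**How many are invited.** With ResearchMatch share *s*, the number invited is 1,500 × (0.2*s* + 1 − *s*) = 1,500 × (1 − 0.8*s*). This gives 300 if *s* = 1, 900 if *s* = 0.5 and 1,500 if *s* = 0. The protocol gives neither *s* nor the proportion who fail or do not book, so the number excluded after allocation cannot be calculated.

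**Is there a gate elsewhere?** The e-couch usage section gives tokens to those who finish baseline and meet all eligibility criteria. The list in 14a does not include the identity check, and 27b names the check separately from 14a. Section 28 says the eligibility and exclusion criteria were updated to cover the check and points to 14a and 25. A condition on tokens would in any case come after the assignment step in section 21.

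**The case against.** The strongest reply is that a gate may exist in practice. Section 27b places the check at the start of the study, section 28 ties it to the updated criteria, and the sequence in section 23 also omits the attention checks, which certainly operate early. Figure 1 and the supplement on protocol changes are not available here. This stands as a reason for caution about what the software does. It does not supply a written gate, because the two sections that define the randomisation trigger name only the baseline batches.

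The second reply is that the route to arm-related bias is narrow. Both arms do the same psychoeducation module in week 1 (15a), and participants learn their arm only after QB2, so non-booking before then cannot reflect arm-specific content or the participant's knowledge of the arm. Mismatches concern information given before randomisation. Not booking forfeits payment, which is an incentive to book in either arm. All of this stands and limits the arm-related part to booking failures after disclosure.

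Third, the main models do not impute outcomes (27c), so keeping non-bookers in the ITT set changes the primary fit little. That is fair. The gain lies in counting them as missing outcomes, by arm, and in bringing them into the sensitivity analyses. Section 27d already promises baseline characteristics of included and excluded participants, but not by arm or by timing.

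Fourth, the trial makes no superiority claim (section 12). True, but the comparisons in 27a and 27d named above still use the randomised groups.

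A reader might infer that the callers are unblinded. The protocol does not say so. Section 24 describes researchers as unblinded for the training-data analysis, section 17 describes the principal investigator as blinded, and the shared database shows possible access only.

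**Conclusion.** The point holds in limited form. As written, the plan permits exclusion after randomisation for failing or not booking the identity check, and then calls the remaining sample intention-to-treat. With an invitation on day 0, the exposure on the fastest path is up to 13 days after allocation, about 6 of them after disclosure. It disappears for booking at seven days per batch or slower. These figures rest on the assumed invitation date and on disclosure about a week after randomisation.

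No count of affected people is supportable. A reader might multiply 1,500 by an assumed half checked and an assumed 5–15% failing, which gives 1,500 × 0.5 × 0.05 = 38 to 1,500 × 0.5 × 0.15 = 113. Both rates are invented for the illustration, and the product treats every failure as occurring after allocation. The subset relevant to arm-related bias, those lost after disclosure, would be smaller again. No sample-size figure in the protocol changes. The amendment is worth making because it is cheap and protects the randomised comparison.

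**What to change.** 1. Make identity check passed, or not required, a condition of the randomisation step in the state machine, and say so in sections 21 and 23.
2. Hide the arm from the staff who run the calls, state this in section 24, and define how many mismatches count as multiple.
3. For participants already randomised before their check, keep in the ITT set anyone removed only for not booking, as a missing outcome covered by the planned sensitivity analyses for data missing not at random. Exclude only for mismatches in information given before randomisation, judged without sight of the arm.
4. Report identity-check exclusions by arm and by timing relative to randomisation and disclosure.
5. Reconcile the text on exclusion after starting the study, sections 21 and 23, the identity-check and e-couch usage parts of section 25, and sections 27b and 28.

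Cost: one condition in existing software, a database view without the arm field, and a few sentences of text. Some invited participants would wait up to about two weeks, which lengthens the gap between the baseline tasks and the intervention, and a few may drop out while waiting. Those losses would come before randomisation, where they do not disturb the comparison between arms.

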#### Study engagement

At any time, we may exclude participants from future portions of the study if they show a significant lack of response and/or involvement in the study components. For example, if a participant does not complete required study components in a timely manner after receiving email reminders, we will inform them that their participation in the study has been discontinued. In such cases, we will compensate participants for all portions they have already completed. If they had already received a token to access e-couch, the token will remain active, and they can continue using e-couch at their discretion.

#### Additional attention checks

We will incorporate task-specific attention checks in each behavioral task to flag participants who did not pay adequate attention in that task. We will perform sensitivity analyses with and without these participants (see section 27d, *Methods for any additional analyses*). The flagging and potential exclusion criteria for analysis of each task are as follows:

Scream task: The scream task includes six audio attention checks in which participants are quietly instructed to press a specific letter key (e.g., “Please press the letter G now”). The purpose of these checks are to ensure minimum audio volume as participants who decreased the volume substantially will not hear the scream. Participants will be excluded if they fail more than two attention checks.Effort task: Participants will be excluded if they timed out in more than 10% of the trials. A trial times out if the participant does not make a choice between the two options within 5 seconds or fails to complete button pressing within 40 seconds on trials requiring effort execution; all timed-out trials are repeated, however, timing out on more than 10% of trials will be grounds for exclusion.Risk task: Participants will be excluded if they require more than five attempts to complete the comprehension check, do not show different risky choice probabilities for the 20% and 80% reward cues or fail to exhibit choice sensitivity to winning 10 versus 0 points.Pavlovian Go/No-Go task: Participants will be excluded if they exhibit chance-level performance (*<* 55% correct responses) on go-to-win trials.Explicit to implicit generalization task: Participants will be excluded if they do not achieve 80% correct response in the initial learning phase.

In addition to initial questionnaire attention checks within the first five minutes of the main study, we will include questionnaire attention checks throughout the entire study to assess data quality and to ensure that participants are reading questions carefully and not replying randomly to self-report instruments.

### Plans to promote participant retention and complete follow-up, including list of any outcome data to be collected for participants who discontinue or deviate from intervention protocols (25b)

We will encourage participants to complete the entire study, including all three follow-up questionnaires, by providing a $10 bonus upon completion of the final follow-up. Participants who withdraw before completing the study will also not receive performance bonuses earned from the behavioral tasks. Automated reminder emails will be sent to participants 7 and 14 days after the start of each follow-up. However, participants may complete each follow-up questionnaire up until the subsequent follow-up is sent out. For the final follow-up questionnaire, participants will have up to three weeks to complete it. For participants who choose to withdraw from the study after commencing it, we will document any reasons they provide by email and securely store this information in our database. When available, we will also record reasons for non-adherence (e.g., discontinuing due to burden or lack of interest) and non-retention (e.g., withdrawal or lost to follow-up). No additional data will be collected from participants who withdraw from the study.

### Data management (26)

We developed software for an automated state machine to track each participant’s progress in the study and to manage study-related email communications. The system sends emails with invitations to specific parts of the study or the self-help tool, as well as reminder emails, based on completion of previous sections and time lags. The state machine runs on a secure server with encrypted file systems. Access is restricted to authorized study members working on this project and IT staff, all of whom must use two-factor authentication. The system records participants’ progress. Eligible participants identified in the screener will receive automatically a main study invitation, while ineligible participants will receive an email informing them that the study is not a good fit for them.

The state machine tracks how long a participant remains in each part of the study and logs every time point at which a participant starts or completes a task or questionnaire set. It also sends reminder emails to participants who do not complete task or questionnaire batches within the allotted time and automatically excludes participants who exceed the grace period, as detailed in section 15c, *Strategies to improve adherence to intervention*. The software also performs random assignment of participants to intervention and training/test groups and distributes e-couch tokens.

We note that the above steps occur automatically, without any involvement or influence from study team members. However, study team members may manually adjust a participant’ progress in the study if the participant requests to skip a task or ask for an extension. Such requests, as well as communication with participants beyond answers to clarification questions and providing payment information, will be documented in the database described below. Any complaints or events requiring IRB involvement will be documented and reported to the IRB through Princeton’s electronic IRB system (eRIA).

The software maintaining the state machine is documented in version-controlled, time-stamped Git repositories. The code includes detailed definition on which data is stored when and how. We also maintain a log of all server updates, including timestamps of new source code commits, their correspondence to IRB-approved protocol modifications and their launch on our server. All these information can be accessed by request. We use Alembic, a database migration tool, to track and apply structured updates to the study’s database, ensuring that all changes to its structure are versioned, documented, and reproducible over time.

